## Abstract

**Background:**

Post-craniotomy pain, relatively common in neurosurgery, is often inadequately managed. Preincisional infiltration with ropivacaine provides effective analgesia for post-craniotomy pain, although its duration of action is limited. Liposomal bupivacaine, a long-acting local anesthetic, can provide analgesia for up to 72 h. However, there is a paucity of research on its efficacy in post-craniotomy analgesia. This study hypothesizes that pre-incisional infiltration with liposomal bupivacaine will demonstrate superior analgesic efficacy compared with ropivacaine in patients undergoing acoustic neuroma surgery.

**Methods:**

This single-center, double-blind, randomized controlled study will recruit 112 patients scheduled to undergo acoustic neuroma surgery. We will compare the effects of liposomal bupivacaine and ropivacaine on postoperative pain when administered via preincisional infiltration before surgery. The primary outcome is the pain score at 24 h postoperatively. Secondary outcomes include the incidence of postoperative nausea and vomiting, amount of postoperative analgesic consumption, changes in vital signs before and after skin incision, and postoperative recovery scale.

**Discussion:**

This randomized controlled trial aims to evaluate the superior effects of pre-incisional infiltration of liposomal bupivacaine on postoperative pain control in patients undergoing acoustic neuroma surgery. This may provide a more effective analgesic regimen for patients undergoing craniotomies.

## 1 Introduction

Treatment for craniocerebral injury or intracranial space-occupying lesions often involves open-cranial surgery, an invasive procedure that inevitably causes pain that is not effectively controlled (1). Many reports have indicated that open-cranial surgery stimulates the scalp, including the soft tissue, muscles, and dura mater, causing varying degrees of pain in patients during the perioperative period, both during and after surgery. Over 60% of patients undergoing open-cranial surgery experience moderate to severe postoperative pain, with the most significant pain occurring between 24–48 h after surgery (2). Furthermore, postoperative pain may have long-term effects on patients. Research has indicated that up to 32% of patients who undergo open-cranial surgery develop chronic pain originating from acute pain. Additionally, 36.7%–49.5% of patients experience persistent pain for up to 12 weeks after surgery; 33%–43% experience persistent pain for more than 1 year; and 28.4% experience persistent pain for more than 3 years (3–5). This phenomenon is primarily attributed to failure to manage acute pain promptly and effectively. Chronic pain can alter the neuroendocrine system, impair postoperative cognitive function, and lead to long-term anxiety. These factors may further result in non-compliance with clinical treatment, thereby adversely affecting patient recovery (6, 7). Effective postoperative analgesia significantly reduces the incidence of complications and lowers disability and mortality rates. Therefore, effective control of pain during and after open-cranial surgery is of great significance for the surgery and prognosis of such patients (8–11). Effective pain control is an essential component of perioperative brain health strategies.

Acoustic neuroma, also known as a vestibular schwannoma, is a common neurosurgical condition requiring open-cranial surgery. It accounts for approximately 5% of intracranial tumors (12). Given the presence of many critical neural structures near the tumor site, such as the facial nerve, monitoring of neural function is typically required during surgery. This ensures that the tumor is removed while preserving facial nerve function, thereby reducing the incidence of postoperative facial paralysis (13–15). However, intraoperative neural function monitoring restricts the use of muscle relaxants and inhalation anesthetics, posing challenges in anesthetic management (16, 17). To avoid adverse situations, such as pain responses and intraoperative awareness, anesthesiologists often administer higher doses of opioid drugs to compensate for the lack of anesthetic depth. However, excessive opioid use can lead to several complications, including respiratory depression, postoperative nausea and vomiting (PONV), hypercapnia, cerebral vasodilation, increased intracranial pressure, and excessive sedation during the recovery and early postoperative periods (18). Given that patients with acoustic neuromas are already at a high risk of PONV, the use of higher opioid doses further increases the incidence of these adverse reactions (19–21). The use of opioid drugs postoperatively can interfere with early neurological examinations. Additionally, severe pain may necessitate their use as rescue rather than routine analgesics. Therefore, to avoid adverse reactions, patients with acoustic neuromas are not advised to receive intravenous postoperative analgesia. The commonly preferred methods are scalp nerve block and local incisional infiltration. However, a scalp nerve block may cause temporary facial nerve paralysis postoperatively, which is not conducive for intraoperative neural monitoring or early neurological assessment of surgical outcomes. This can directly delay the surgeon’s ability to judge the patient’s condition and may negatively affect recovery (22, 23). Therefore, optimal local incisional infiltration is considered the most favorable pain management method for patients undergoing acoustic neuroma surgery (24). Ropivacaine and bupivacaine are commonly used as local anesthetics for local incisional infiltration in clinical practice. Ropivacaine is an amide-type local anesthetic that is known for its good analgesic effects, minimal adverse reactions, and low cardiac toxicity. However, its duration of action is relatively short (2–6 h), which is insufficient to cover the patient’s entire pain period (25). Bupivacaine is a widely used long-acting local anesthetic with a duration of action of 6–8 h. However, it has higher cardiac toxicity, and its duration of action is insufficient to meet the clinical needs for postoperative analgesia (26). In 2011, the U.S. Food and Drug Administration approved a multilayered, foam-based bupivacaine liposome injection (trade name: Exparel) based on Depo Foam™ technology (27). This formulation encapsulates local anesthetics in a drug delivery system to provide long-lasting analgesia for surgical patients, with effects lasting up to 72 h (28). Bupivacaine liposomes can significantly improve postoperative analgesia in orthopedic, gynecological, abdominal, and plastic surgeries and are safe (29–31).

Pain associated with systemic hypertension, anxiety, and vomiting can also lead to intracranial hypertension. This condition is difficult to distinguish from postoperative neurosurgical complications and may mask or exacerbate related symptoms. Poor pain control progressing to chronic pain can lead to long-term mental anxiety and tension, potentially affecting cognitive function and hindering recovery. Effective postoperative analgesia can reduce the incidence of adverse reactions and complications following surgery. Bupivacaine liposome, a new local anesthetic, has a duration of action of up to 72 h. Administering it via local infiltration at the incision site before surgery can provide analgesia that covers the pain following open-cranial surgery, potentially providing better postoperative analgesia, reducing postoperative complications, and promoting early recovery. A recent meta-analysis by Fiore et al., the largest to date on craniotomy analgesia, provides high-certainty evidence that non-steroidal anti-inflammatory drugs and acetaminophen reduce pain 24 h postoperatively and that ropivacaine scalp block provides effective analgesia within the first 6 h after surgery (32). However, its limited duration of action fails to cover the peak pain period occurring 24–48 h post-craniotomy (2, 6). Therefore, our study seeks to build upon this foundation by evaluating whether pre-incisional infiltration with liposomal bupivacaine, which can provide analgesia for up to 72 h (33), offers superior and sustained pain control compared with ropivacaine, potentially bridging this critical analgesic gap.

This study aims to compare the effects of ropivacaine and liposomal bupivacaine for pre-incisional local infiltration on perioperative pain in patients undergoing acoustic neuroma surgery. Additionally, this study will evaluate opioid and other analgesic consumption, postoperative hospital stay, recovery, and the incidence of postoperative complications between the two groups. This study aims to provide a reference for optimizing anesthetic and analgesic regimens in patients with acoustic neuroma during the perioperative period.

## 2 Methods and analysis

### 2.1 Study design

This trial is a prospective, single-center, randomized, double-blind clinical study designed in accordance with Standard Protocol Items: Recommendations for Interventional Trials reporting guidelines (32). Participants will be randomly assigned to either the liposomal bupivacaine (group B) or liposomal bupivacaine (group C) group in a 1:1 allocation ratio. The trial will be conducted at Shanghai General Hospital, China, in October 2024. The schedules for enrollment, allocation, and assessment are shown in Table 1. A flow diagram of this trial is shown in Figure 1.

**TABLE 1 T1:** The schedule of enrollment, allocation and assessments.

	Enrollment	Allocation	Post operation				Close-out
Timepoint	−1 day	0 day	PACU	24 h	48 h	72 h	
**Enrollment:**							
Eligibility screen	×						
Informed consent	×						
Allocation		×					
**Intervention:**							
Ropivacaine group (group C)		×					
Liposomal bupivacaine group (group B)		×					
**Assessment:**							
Base line	×	×					
MAP and HR		×					
Sufentanil dose		×	×				
Use of other analgesics		×	×	×	×	×	
Pain VAS			×	×	×	×	
PONV score				×	×	×	
Extubation time and PACU stay			×				
QoR-15						×	
Complications			×	×	×	×	
Adverse events			×	×	×	×	
Costs							×

HR, heart rate; MAP, mean arterial pressure; VAS, visual analog scale; PONV, postoperative nausea and vomiting; PACU, post-anesthesia care unit; QoR-15, quality of recovery-15; h, hour.

**FIGURE 1 F1:**
[figure not shown]
Flow diagram of this trial.

### 2.2 Objectives

The main objective of this trial is to implement preemptive analgesia through pre-incisional infiltration with bupivacaine liposomes. We aim to investigate the effects of this method on patients’ pain scores from 1 to 3 days postoperatively and to assess the patients’ reactions to skin incision, opioid consumption, and quality of recovery, with the ultimate goal of validating the superiority of pre-incisional infiltration with bupivacaine liposome in postoperative pain management in patients undergoing acoustic neuroma surgery.

### 2.3 Recruitment and ethics

This study has been approved by the Ethics Committee of Shanghai General Hospital and registered with the Chinese Clinical Trial Registry (ChiCTR2400090509; Principal investigator: [name]; Registration Date: October 8, 2024). The trial protocol has been modified twice, with the final version being V3.0/20240715. This trial does not involve the collection of biological samples. Patients scheduled for acoustic neuroma surgery will be recruited and screened by the investigators 1 day prior to surgery. Those who meet the inclusion criteria will be scheduled for a subsequent interview, during which they will receive an informed consent discussion and will sign an enrollment form.

### 2.4 Eligibility criteria

#### 2.4.1 Inclusion criteria

(1)   Age >18 years(2)   Scheduled for elective acoustic neuroma surgery(3)   American Society of Anesthesiologists (ASA) physical status I-III(4)   Inform the relevant contents of this clinical trial and sign the informed consent

#### 2.4.2 Exclusion criteria

(1)   Combination of severe cardiopulmonary, hepatic, or renal dysfunction(2)   History of mental illness or current use of psychotropic medications(3)   History of neurological diseases (e.g., cerebral infarction, transient ischemic attack, cerebral hemorrhage, Parkinson’s disease, intellectual disability, or craniocerebral injury).(4)   Heart rate (HR) <50 bpm or prolonged QT interval on electrocardiogram (ECG)(5)   ECG indicating pre-excitation syndrome or confirmed history thereof(6)   Allergy to ropivacaine or bupivacaine liposome(7)   Puncture site or systemic infection(8)   History of craniotomy(9)   Postoperative sedation for any reason.(10)   Inability to understand visual analog scores (VAS)(11)   Refusal to sign informed consent

#### 2.4.3 Withdrawal criteria

(1)   Delayed extubation after surgery or admission to the intensive care unit with endotracheal intubation(2)   Need for second operation within the postoperative operation(3)   Poor postoperative cognitive function within 72 h

### 2.5 Randomization and blinding

In this study, the method of randomization is block randomization. The block length is eight, and patients will be randomly assigned in a 1:1 ratio to either the liposomal bupivacaine or ropivacaine group. After designing the serial numbers according to the blocks, the numbers will be arranged in ascending order both within and across the blocks. An envelope is encoded for each number. The allocation sequences will be placed in sequentially numbered opaque sealed envelopes. On the day of surgery, a nurse will open the envelope to prepare the solution according to the protocol. The prepared solution will be placed in a light-protected syringe and administered by a neurosurgeon. Participant recruitment will be conducted by an anesthesiologist who will not be involved in data collection and analysis. Upon unblinding, the envelopes will be opened in a strict numerical order. The envelopes will be managed by a certified nurse who will not be involved in any other aspect of the study, beyond managing the envelopes, unblinding the participants, and dispensing medication. Given the single type of surgery and the single-center nature of the study, stratification is deemed impractical. Additionally, the surgical procedure for acoustic neuroma surgery is standardized, with patients usually positioned laterally, and the surgical approach is typically through the sigmoid sinus. A relatively fixed incision area ensures better intervention consistency.

The participants, investigators, and evaluators will be blinded to the study procedure. Owning to the distinct properties of the two drugs, the bupivacaine liposome injection solution appears as a white suspension, whereas the ropivacaine injection solution is a colorless transparent liquid-dark; hence, a light-resistant syringe will be used during dispensing to maintain blinding. This prevents the identification of the agent from the outside. The surgeon is responsible only for scalp injections and will not participate in screening, enrollment, surgical anesthesia, or follow-up. Researchers involved in screening, enrollment, surgical anesthesia, and follow-up, including the patients themselves, will be unaware of the grouping.

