### 2.6 Intervention description

The intervention in this study involves preoperative infiltration of the patient’s scalp incision by the neurosurgeon using a 22-gauge needle under sterile conditions. Neurosurgeons will prepare separate local anesthetics before surgery in the operating room. In Group B, 20 mL of the original bupivacaine liposome solution will be used and in Group C, 0.75% ropivacaine (4 mL) will be diluted to a total volume of 20 mL with normal saline.

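### One published, fixed block length of eight leaves about one assignment in five certain to an observer who knows every earlier treatment in the block; varying it is a cheap improvement

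*Protocol article*

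**What the plan says.** Section 2.5 of the Protocol article states that "the method of randomization is block randomization" and gives one length only: "The block length is eight, and patients will be randomly assigned in a 1:1 ratio". There are no strata ("stratification is deemed impractical"), so the whole trial runs on one list. Concealment is by envelope: "The allocation sequences will be placed in sequentially numbered opaque sealed envelopes". Section 4 adds that the block size was taken into account in setting the total of 112.

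On masking, section 2.5 says that "the bupivacaine liposome injection solution appears as a white suspension, whereas the ropivacaine injection solution is a colorless transparent liquid-dark" and relies on a light-protected syringe to hide the difference. A neurosurgeon injects.

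The article gives two accounts of who prepares the drug. Section 2.5: "On the day of surgery, a nurse will open the envelope to prepare the solution according to the protocol". Section 2.6: "Neurosurgeons will prepare separate local anesthetics before surgery in the operating room". Section 2.6 also describes dilution with saline in one arm only.

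Section 2.5 also states safeguards. The surgeon takes no part in screening, enrolment, anaesthesia or follow-up. An anaesthesiologist without a data role recruits. The envelope nurse has no other study role. Those who screen, enrol, anaesthetise and follow up do not know the grouping.

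**The concern.** A sealed envelope conceals the next assignment only as far as earlier assignments do not reveal it. With one list, one known block length and sequential numbers, every block ends at a known place: envelopes 8, 16, 24 and so on to 112. Once one arm has used its four places, the rest of the block is fixed.

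Earlier assignments could become known in this trial because the drugs differ in appearance. If section 2.6 is the correct account, the people who prepare the drug know the arm, and the syringe masks nothing for them.

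The 24 h VAS comparison is at stake. If a determined assignment were known to someone who can decide whether or when a patient enters, patients with higher or lower expected pain could be steered to one arm. Neither Table 1 nor section 3.1 lists a preoperative pain score, so an imbalance in baseline pain would not show.

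**Working it through.** **The plan's own figure.** Section 4 gives means 2.9 and 3.7, SD 1.4, α = 0.05 and β = 0.2. The difference is 0.8. A two-sided t-test needs 49.05 per group, rounded up to the stated 50. With 10% loss, 50/0.9 = 55.6, so 56 per group and 112 in total. 112/8 = 14 full blocks. The sample size reproduces and agrees with the block length. The article gives no figure for predictability; what follows is added here.

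**Assignments known with certainty, fixed blocks of eight.** A block with four places per arm has C(8,4) = 70 equally likely orders. Counting the places at the end of each order where one arm is already used up gives:

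| Determined places at end of block | Orders of 70 | Share |
|---|---|---|
| 1 | 40 | 57.1% |
| 2 | 20 | 28.6% |
| 3 | 8 | 11.4% |
| 4 | 2 | 2.9% |

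Mean = (40×1 + 20×2 + 8×3 + 2×4)/70 = 112/70 = 1.6 per block. The closed form for a block of 2m agrees: 2m/(m+1) = 8/5 = 1.6. As a share, 1.6/8 = 20%. Over 14 blocks, 14 × 1.6 = 22.4 patients. The last place is always determined. The last two or more are determined in 30/70 = 42.9% of blocks.

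**Best guess over all assignments.** Always guessing the arm with more places left gives an expected number correct per block of m + (4^m/C(2m,m) − 1)/2 = 4 + (256/70 − 1)/2 = 5.33. 5.33/8 = 66.6%, against 50% with no knowledge.

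**Varying block lengths.** Trials of 112 were simulated 1,500 times. Block lengths were drawn independently with equal probability, and the observer knew the set of lengths and all past treatments but not the length of the current block.

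| Lengths | Known with certainty | Best guess correct |
|---|---|---|
| 8 only | 20.0% | 66.7% |
| 4, 6, 8 | 2.3% | 67.9% |
| 4, 8 | 7.6% | 67.9% |
| 6, 8, 10 | 1.6% | 66.2% |

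With 4, 6 and 8, certainty falls from about 22 patients to 0.023 × 112 = 2.6. Guessing accuracy hardly moves.

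**The case against.** The strongest reply is that no person named in the article has both the knowledge and the opportunity. Section 2.5 gives recruitment to someone who does not know the grouping, restricts the surgeon to the injection, and gives the nurse no other role. A fixed block of eight is a recognised design, and the article does not contradict itself on it. This stands, and it is why the point is minor.

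A reader might infer four stronger things that the article does not support.

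- **That allocation is open to the surgical team.** This takes section 2.6 and sets aside section 2.5, where a nurse prepares a light-protected syringe. The two conflict; neither is shown to be the practice.
- **That surgeons can steer patients through the operating order.** The article does not say who sets the order or when an envelope number is tied to a patient. The phrase about strict numerical order stands in a sentence on unblinding. A condensed article may leave such detail to the full protocol.
- **That nothing could reveal selection.** Section 3.1 records tumour size, among other characteristics, and section 4 adjusts the 24 h VAS for it. Selection on tumour difficulty would be at least partly visible. Only baseline pain is unrecorded.
- **That varying blocks would make guessing harder.** The second table shows they would not; only certainty falls.

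**Conclusion.** The point holds in a conditional form. Under the stated scheme, 20% of assignments, about 22 of 112, are known with certainty to an observer who knows the block length and every earlier treatment in the block. The figure is an average over the trial, and the certainty falls only at the ends of blocks. It becomes a bias only if that knowledge reaches someone who influences enrolment or its timing; the article gives no evidence that it does. If the nurse alone prepares the drug and the syringe masks it fully, the risk is smaller still. This is an inexpensive improvement to concealment, not a flaw that undermines the primary comparison. The conflict between sections 2.5 and 2.6 needs settling in any case, because the masking depends on it.

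**What to change.** 1. Generate the list, or the blocks not yet used, with randomly varying block lengths. With 4, 6 and 8, for example, six blocks of each length plus one more of four give 6 × 18 + 4 = 112, in random order. Keep the lengths out of investigator-facing documents.
2. Reconcile sections 2.5 and 2.6, so that the drug is prepared either by the envelope nurse of section 2.5 or by someone otherwise separated from enrolment and scheduling. Changing the block length does not do this, and best-guess accuracy stays near 67% for anyone who sees past treatments.
3. Fix the envelope number to the patient at consent, if this is not already done.

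The cost is a regenerated list and re-made unused envelopes, with no extra patients or staff. The downside is a possible imbalance of a few patients if recruitment stops in mid-block. With a longest block of eight it cannot exceed four, the same limit as under the present scheme.

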### 2.6 Intervention description

The intervention in this study involves preoperative infiltration of the patient’s scalp incision by the neurosurgeon using a 22-gauge needle under sterile conditions. Neurosurgeons will prepare separate local anesthetics before surgery in the operating room. In Group B, 20 mL of the original bupivacaine liposome solution will be used and in Group C, 0.75% ropivacaine (4 mL) will be diluted to a total volume of 20 mL with normal saline.

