## 8 Harms

The treatment measures in this study involve the use of local anesthetics for incisional infiltration. There is a risk of local anesthetics entering blood vessels. To mitigate this risk, the syringe is routinely aspirated before the procedure to confirm the absence of blood before proceeding with incision infiltration. However, the concentration of the drugs used in this trial is low, and the dose is small. The physicians performing the procedures are highly skilled, and the administered dose is well below the threshold that can cause local anesthetic toxicity. In the event of accidental symptoms of local anesthetic toxicity or circulatory fluctuations, immediate symptomatic treatment will be administered, and adverse events will be recorded. Adverse events related to study interventions will be treated for free.

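### Sections 2.5 and 2.6 name different people to prepare two visibly different drugs; following 2.6 unblinds the neurosurgeon and puts the blinding of operating-room staff at risk

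*Protocol article*

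**What the plan says.** Section 2.5 (Randomization and blinding) sets out one handling chain. The nurse comes first: "On the day of surgery, a nurse will open the envelope to prepare the solution according to the protocol". The surgeon then receives a finished product: "The prepared solution will be placed in a light-protected syringe and administered by a neurosurgeon". The nurse is kept apart from the rest of the trial: "The envelopes will be managed by a certified nurse who will not be involved in any other aspect of the study", apart from handling envelopes, unblinding and dispensing. The section acknowledges that the two products look different, one a white suspension and the other clear and colorless. It relies on the light-resistant syringe to hide this: "This prevents the identification of the agent from the outside". It confines the surgeon to the scalp injection and keeps the surgeon out of screening, enrollment, anesthesia and follow-up.

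Section 2.6 (Intervention description) states instead: "Neurosurgeons will prepare separate local anesthetics before surgery in the operating room". It then describes how each arm's 20 mL is made up. The liposomal product is used as supplied, and 4 mL of ropivacaine is diluted with saline.

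Section 5 (Data collection) requires the intraoperative anesthesiologists and the follow-up researchers to be blinded. Section 8 (Harms) describes a precaution at injection: "the syringe is routinely aspirated before the procedure to confirm the absence of blood".

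**The concern.** Because the drugs cannot be made to look alike, the blind depends on filling the syringe where nobody who must stay blinded can see it. Section 2.5 assigns that step to a person with no other role. Section 2.6 assigns it to the operating team, in the operating room. Site staff who follow 2.6 would be complying with the protocol while bypassing its only masking step.

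What is at stake is mainly intraoperative. Under section 2.7 the anesthesiologist adjusts remifentanil within a range, chooses the pre-incision sufentanil dose within a range, and responds to sympathetic excitation. Section 3.3 makes mean arterial pressure and heart rate at five time points, and intraoperative opioid use, secondary outcomes. An anesthesiologist who knew the arm could, without meaning to, change both the co-treatment and the outcomes measured.

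**Working it through.** The protocol gives no figure for this point and no arithmetic decides it. The check sets the statements side by side.

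1. **Who prepares.** Section 2.5: a nurse, after opening the envelope. Section 2.6: neurosurgeons. These are different people for the same task.
2. **Where.** Section 2.6: in the operating room. Section 2.5 names no place.
3. **What the surgeon does.** Section 2.5: injects only. Section 2.6: prepares as well. This is a second conflict, independent of the first.
4. **Does preparation reveal the arm?** Yes, in two ways. Section 2.5 says the products look different. Section 2.6 has one product diluted and the other not. The dilution is a real step: 4 mL × 0.75% / 20 mL = 0.15%, the ropivacaine concentration given in section 9.
5. **Who would learn the arm under 2.6?**
   - The preparing neurosurgeon: certain. The masked syringe then hides nothing from that person.
   - The intraoperative anesthesiologist: possible. This person works in that room and must be blinded under sections 2.5 and 5. The document does not say whether the anesthesiologist is present for the preparation or could see it.
   - The patient and the follow-up researchers who collect the 24 h pain score: nothing in 2.6 reveals the arm to them.
6. **Which outcomes are exposed if the anesthesiologist sees it?** Of the five hemodynamic time points in section 3.3, four (incision, drilling, skin closure, end of operation) come after a pre-incision injection. Intraoperative opioid use is exposed in the same way.
7. **Syringe and aspiration.** Section 2.5 needs the contents not to be identifiable from outside. Section 8 needs the operator to establish that no blood has been drawn back. The article does not say how one syringe serves both purposes. This is a tension and not a contradiction: the syringe is described as light-protected or light-resistant, and section 8 does not say that blood must be seen through the barrel.

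**The case against.** The strongest reply is that the blind described in section 2.5 covers participants, investigators and evaluators, together with the researchers in screening, enrollment, anesthesia and follow-up. The surgeon is not on that list and is kept out of those activities. An unblinded surgeon is therefore not in itself a breach of the stated blind. This stands, and it limits the consequence. It does not remove the conflict over who prepares the drug, or the effect of moving preparation into the operating room.

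Second, discretion is limited. Remifentanil is titrated to keep pressure and heart rate within 20% of baseline, and postoperative rescue is triggered by a pain score. This stands in part: such rules narrow the room for biased decisions but do not close it, because doses within the ranges are still chosen.

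Third, the word for preparing in 2.6 might loosely mean laying out a syringe that the nurse has already filled. That reading would restore agreement, but the sentence does not say so, and the make-up of each solution follows directly after it.

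A reader might go further than the document allows in three ways:

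- **That the double blind fails as a whole, including for the primary outcome.** The document shows no route from 2.6 to the patient or the 24 h pain assessor.
- **That the fixed block ("The block length is eight, and patients will be randomly assigned in a 1:1 ratio") lets staff deduce later allocations and so select patients.** That needs someone who enrolls patients to have seen the earlier allocations. The person certain to have seen them under 2.6 is the surgeon, who is barred from enrollment, and the envelopes are opaque, sealed and sequentially numbered. A leak to the recruiting anesthesiologist is conceivable but not shown.
- **That an unblinded surgeon biases length of stay through discharge decisions.** The document does not say who decides discharge.

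**Conclusion.** The contradiction is definite: sections 2.5 and 2.6 assign drug preparation to different people, and 2.6 also breaks the limit that 2.5 puts on the surgeon's role. If 2.6 is followed, the neurosurgeon knows the arm for each patient so handled, up to all 112 planned. For the anesthesiologist and other operating-room staff, unblinding is a risk and not an established fact. It rests on the assumption that they are present and able to see the preparation. On that assumption, intraoperative hemodynamics and opioid use are open to bias of a size that cannot be estimated from the document. The 24 h pain score is not shown to be affected. The point should be corrected because the masking depends on this one step and the correction is simple.

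**What to change.** Replace the 2.6 sentence. The new text should say that the nurse already assigned in 2.5 prepares both solutions out of sight of operating-room study staff and hands over the filled, masked syringe. State the injecting neurosurgeon's blinding status explicitly, whether blinded or potentially unblinded, so that the double-blind description can be read accurately. In the same handling instruction, explain how the masked syringe of 2.5 is compatible with the aspiration check of section 8; the two passages must be reconciled, and how is for the investigators to decide.

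The cost is a short protocol correction and a handling instruction for a nurse who already has the task. No extra staff, change to the allocation list or change to the sample size is needed.
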